### Sample Size Calculation

The current incidence of PRS at our center is 30%. Assuming a 50% decrease in PRS incidence (from 30% to 15%) with an α risk of 5% and a power of 80%, bilateral testing, and the Fleiss correction with a 10% loss rate, we require 268 participants (134 in each group). Due to the limited number of transplants per year in our center, achieving such a large sample will take 6-8 years. Given that this study will be conducted at a single center, the projected patient enrollment is 35 individuals per year, resulting in a final sample size of 70 participants. To attain 80% power with this sample, it is necessary to achieve a complete elimination of PRS. Although it is unlikely that such a reduction in the incidence of PRS would be achieved, we believe that this is a reasonable number of participants to show differences in the primary outcome that, although not reaching the desired statistical significance, would serve to justify a future multicenter randomized controlled trial. Participants will be randomly assigned to groups using a computer-generated sequence created by SPSS Statistics (SPSS Inc). The computer-generated sequence will allocate 35 participants to the ascorbic acid intervention group and 35 participants to the saline control group. To ensure independence, an unrelated staff member will enroll patients and prepare medication or saline upon arrival.

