### Strength and Limitation of the Study

The main limitation of the study, due to the limited number of participants planned, is that it may not achieve adequate statistical power to establish with sufficient scientific evidence whether vitamin C reduces the PRS and improves the results of LT. However, we believe that if positive results in favor of vitamin C are obtained, the trial would serve as the basis for a larger trial involving other transplant centers, which would allow us to demonstrate the benefit of vitamin C with enough statistical power. It is possible that we may not be able to control for additional variables that may bias the results, including those related to the surgical and anesthesia teams. A forthcoming multicenter trial could address this issue.

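### With 70 patients, 80% power does not require eliminating PRS: a fall from 30% to about 5% is enough, while power for the assumed fall to 15% is about 32% and is not stated

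*Protocol article*

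**What the plan says.** Protocol article, Sample Size Calculation: the centre's PRS incidence is put at 30%, and the planned effect is a halving to 15%, "with an α risk of 5% and a power of 80%, bilateral testing", using "the Fleiss correction with a 10% loss rate". This leads to 268 participants, 134 per group. The article then judges that number unattainable at one centre, sets the sample at 70 (35 per group), and describes what that sample can do in one sentence: "To attain 80% power with this sample, it is necessary to achieve a complete elimination of PRS". It goes on to say that such a reduction is unlikely and that differences short of significance could still justify a multicentre trial.

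The Analysis section names the chi-square test for PRS, with all randomised participants as the primary population. It does not say whether a continuity correction is applied.

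Strength and Limitation of the Study returns to power only in general terms: "it may not achieve adequate statistical power to establish with sufficient scientific evidence whether vitamin C reduces the PRS". Neither section gives the power of 70 patients for the fall from 30% to 15%.

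**The concern.** A comparison of 30% with 0% is a very large contrast for 35 patients per group. If the treated group has no events, the uncorrected chi-square test is significant at 5% with 4 or more events among 35 controls, and Fisher's exact test with 6 or more. The expected control count is 0.30 × 35 = 10.5. Power should therefore be well above 80%, and something short of elimination should be enough for 80%.

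Two things are at stake. The sentence misstates the detectable effect of the trial that is being run. It also stands where the more useful figure belongs, namely the power for the effect that the investigators themselves assumed. Without that figure a reader cannot judge how often a true halving of PRS would give a non-significant result. The multicentre argument also depends on a correct detectable effect and on the expected precision.

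**Working it through.** **Inputs (Sample Size Calculation).** p1 = 0.30; assumed p2 = 0.15; two-sided α = 0.05 (z = 1.960); 80% power (z = 0.842); Fleiss continuity correction; 10% loss; 35 per group. After 10% loss, 35 × 0.9 = 31.5, so 31 or 32 per group.

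**1. The article's own 134 per group.** With p̄ = (p1 + p2)/2 and d = p1 − p2:

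n = [1.960·√(2p̄(1−p̄)) + 0.842·√(p1(1−p1) + p2(1−p2))]² / d²

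For 30% v 15% this is 120.5, so 121 per group. The Fleiss correction, n/4 × [1 + √(1 + 4/(n·d))]², gives 133.5, so 134. The printed 134 therefore matches the correction without a loss allowance, or 121 × 1.1 = 133.1 (134) without the correction. Both together give 134/0.9 = 148.9, so 149 per group, 298 in total. That is a separate inconsistency. It does not affect what follows, but it confirms the family of formulas in use.

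**2. Sample size for complete elimination (p2 = 0).** The same formulas give 21.02 (22 per group) uncorrected and 27.3 (28 per group) corrected. Allowing for loss, 28/0.9 = 31.1, so 32 per group or 64 in total. Even with both adjustments this is below 70.

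**3. Power at 35 per group for 30% v 0%.**

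Power = Φ[(d − 1.960·s0)/s1], with s0 = √(2p̄(1−p̄)/n) and s1 = √((p1(1−p1) + p2(1−p2))/n)

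s0 = √(2 × 0.15 × 0.85/35) = 0.0854; s1 = √(0.21/35) = 0.0775. (0.30 − 1.960 × 0.0854)/0.0775 = 1.71, so power is 95.7%. With the continuity correction d becomes 0.30 − 1/35 = 0.2714, the argument is 1.34 and power is 91.1%.

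**4. Power at 35 per group for 30% v 15%.** s0 = 0.0998, s1 = 0.0982. (0.15 − 1.960 × 0.0998)/0.0982 = −0.465, so power is 32.1%. Corrected, with d = 0.1214, it is 22.5%.

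**5. All variants.** The exact rows sum binomial probabilities over every possible pair of event counts. The last column is the treated-arm incidence at which power equals 80%.

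| Per group | Method | Power, 30% v 0% | Power, 30% v 15% | Incidence for 80% power |
|---|---|---|---|---|
| 35 | formula, uncorrected | 95.7% | 32.1% | 5.0% |
| 35 | formula, corrected | 91.1% | 22.5% | 2.8% |
| 35 | exact, chi-square | 99.8% | 31.7% | 5.8% |
| 35 | exact, Yates or Fisher | 97.3% | 23.3% | 3.9% |
| 31–32 | formula, uncorrected | 93.1–93.9% | 29.0–29.7% | 3.8–4.1% |
| 31–32 | formula, corrected | 86.3–87.7% | 19.4–20.2% | 1.5–1.8% |
| 31–32 | exact, chi-square | 99.3–99.5% | 29.3–30.5% | 4.9–5.1% |
| 31–32 | exact, Yates or Fisher | 93.7–94.9% | 19.3–21.5% | 2.5–2.9% |

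No row gives 80% at complete elimination; the lowest value is 86.3%.

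**6. Expected precision.** At 30% v 15% with 35 per group, the half-width of the 95% CI for the risk difference is 1.96 × √(0.21/35 + 0.1275/35) = 0.192, or about 19 percentage points, against an assumed difference of 15.

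**The case against.** The strongest reply is that the sentence is loose rather than misleading. With the article's own continuity correction and 10% loss, the 80% threshold is a treated-arm incidence of 1.5 to 1.8% by formula (2.5 to 2.9% exact), which is less than one expected event in 31 or 32 patients. Complete elimination can be read as a rounding of that. The error is also conservative, since it makes the trial look weaker at large effects and does not flatter the design. The sample was set by feasibility, not by this sentence. The shortfall is disclosed as well: 268 against 70, an effect conceded to be unlikely, and power named as the main limitation. On this view the missing power at 15% is only an omission from a condensed article.

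Much of this stands. The picture of a severely underpowered trial does not change, no test or decision rule depends on the sentence, and the 32% is the top of a range that reaches about 19%. Those points bear on how heavily the error should weigh.

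They do not make the sentence true. It says elimination is necessary, and no variant supports that. For the test and population named in the Analysis section, an uncorrected chi-square on all randomised patients needs a fall to about 5 or 6%, a relative reduction of 81 to 83%. A general admission of low power does not correct a specific wrong figure, and it does not tell the reader that power for the assumed effect is 32% or less.

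**Conclusion.** The concern holds. With 35 per group, 30% control incidence and a two-sided 5% test, complete elimination of PRS gives 91 to 99.8% power depending on the method, and at least 86% with correction and 10% loss. The treated-arm incidence that gives 80% power is about 5 to 6% (uncorrected chi-square, all 70 evaluable), about 3 to 4% (corrected), or 1.5 to 3% (corrected, with loss).

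Power for the assumed fall to 15% is about 32% for the uncorrected chi-square test with all 70 evaluable, 22 to 23% with a correction or Fisher's test, and 19 to 22% with loss as well. A true halving of PRS would thus be missed about two times in three at best, and about four times in five under the least favourable conventions.

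These results rest on the article's 30% control incidence and equal allocation. The statement is wrong as written and should be corrected. Because the error is conservative and low power is openly acknowledged, the consequence lies in how the results are interpreted, not in the validity of the analysis.

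**What to change.** Replace the sentence in Sample Size Calculation with text that names its conventions, for example:

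> With 35 evaluable patients per group, a control incidence of 30% and a two-sided 5% level, the uncorrected chi-square test has 80% power to detect a fall to about 5% (about 3–4% with a continuity correction) and about 32% power for the assumed fall to 15% (about 23% with a continuity correction). With 10% loss and a continuity correction these become about 1.5–3% and 19–22%. The expected half-width of the 95% CI for the risk difference at 30% versus 15% is about 19 percentage points.

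Adjust the next sentence, which calls the required reduction unlikely, so that it refers to the corrected figure. In Strength and Limitation of the Study, give the 32% (range 19–32%) beside the general remark on power. State in the Analysis section whether the chi-square test is continuity-corrected, so that the quoted power matches the test.

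The cost is wording only: no extra patients and no change to the endpoint or populations. One disclosed figure becomes more favourable (the detectable effect), and one unfavourable figure (power at 15%) is disclosed for the first time.

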### Trial Design

This study is designed as a single-center, double-blind, randomized controlled trial. Participants will be randomized to receive ascorbic acid (intervention group) or saline (0.9%; control group). We will conduct a superiority analysis.

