### Study Procedures and Intervention

The intervention group will receive a dose of 1500 mg of intravenous ascorbic acid (vitamin C) diluted in 100 mL of 0.9% saline for 30 minutes, to be administered during the anhepatic phase of liver transplantation.

The control group will receive a dose of 100 mL of 0.9% saline for the same period and under the same conditions.

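### One staff member both enrols patients and prepares the unblinded infusion, so the procedure as written does not assure allocation concealment

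*Protocol article*

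**What the plan says.** The randomisation text stands in the Protocol article under Sample Size Calculation. The list is produced by software: "Participants will be randomly assigned to groups using a computer-generated sequence created by SPSS Statistics (SPSS Inc". Its totals are fixed: "The computer-generated sequence will allocate 35 participants to the ascorbic acid intervention group and 35 participants to the saline control group". The next sentence gives the safeguard and the person who carries it out: "an unrelated staff member will enroll patients and prepare medication or saline upon arrival". The stated purpose is independence; the text does not say from whom.

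Under Study Procedures and Intervention, the active product is "1500 mg of intravenous ascorbic acid (vitamin C) diluted in 100 mL of 0.9% saline for 30 minutes". For the comparator, "The control group will receive a dose of 100 mL of 0.9% saline for the same period and under the same conditions". Under Trial Design: "This study is designed as a single-center, double-blind, randomized controlled trial".

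**The concern.** Allocation concealment means that whoever decides on a patient's entry cannot know or predict that patient's arm. The usual protection is to keep enrolment apart from any task that reveals allocations. Here the article puts both tasks in one role. It describes a safeguard, but that safeguard serves a different purpose: an outsider who makes up the infusion helps keep clinicians and assessors blind, yet is not blind while enrolling the next patient.

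If entry or its timing can depend on a known or guessed arm, the groups may differ in prognosis before treatment starts. Blinding and intention-to-treat analysis apply only to patients already entered. The planned adjustment for baseline factors that differ at P≤.20 can deal only with what was measured. This matters in a trial of 70 whose authors say, under Sample Size Calculation, that a difference short of significance would still support a multicentre trial. A modest difference is what selective entry could produce.

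**Working it through.** The plan gives no figure on this point to reproduce. The check has three steps: what follows from the text, how predictable the next assignment is, and how much a few selective entries could matter.

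**1. What follows from the text**
- One role enrols and prepares (Sample Size Calculation).
- One product contains ascorbic acid and the other is saline alone (Study Procedures and Intervention). Preparing a product therefore requires that patient's arm.
- So, while still enrolling, this person knows all earlier arms.
- The article does not say who holds the list, or whether an assignment is released before or after entry.

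**2. Predictability of the next assignment**

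Inputs: m = 35 per arm, 2m = 70 (Sample Size Calculation). Assume the enroller sees past arms only, the list is a random ordering with fixed totals and no blocks, and the enroller always guesses the arm with more places left (the Blackwell-Hodges convergence strategy).

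- Expected correct guesses = m + (2^(2m) / C(2m, m) − 1) / 2.
- 2^70 / C(70, 35) = 10.52, so the result is 35 + (10.52 − 1) / 2 = 39.76.
- 39.76 / 70 = 56.8%, against 50% by chance. An exact recursion over the places left in each arm gives the same value.
- Expected number of assignments certain in advance, because one arm is already full: 2m / (m + 1) = 70 / 36 = 1.94. These fall at the end of the list.

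Range over what the article does not state:

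| What the enroller knows | Correct guesses |
|---|---|
| Past arms, fixed 35:35 total, no blocks | 56.8% |
| Past arms, known fixed blocks of 10 (assumed) | 65.3% |
| Blocks of 8 (assumed) | 66.6% |
| Blocks of 6 (assumed) | 68.3% |
| Blocks of 4 (assumed) | 70.8% |
| Blocks of 2 (assumed) | 75.0% |
| The list itself before entry (not stated) | 100% |

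The block rows are assumptions only; the article mentions no blocks.

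**3. Upper-bound illustration of the effect on the primary outcome**

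With 35 per arm, one PRS event is 1 / 35 = 2.9 percentage points. If selective entry replaced two patients who would have had PRS with two who would not, that arm's observed rate would move by 2 / 35 = 5.7 points. The effect in the plan's sample size calculation is 30% − 15% = 15 points, and 5.7 / 15 = 38% of it. Two is an arbitrary number, and the sum supposes that both substitutions change the outcome. It bounds what two such entries could do and does not estimate the bias.

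**The case against.** The strongest reply is that nothing in the article shows allocation to be exposed. Preparing one infusion needs only the current patient's arm, and that could be released after the patient is entered. Sealed envelopes, pharmacy release or a central service are details that a journal article commonly leaves to the full protocol, so silence about them is no fault. This stands. A reader might infer that the staff member holds the list, knows the next assignment and that concealment has failed. The documents do not say so.

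The fixed 35:35 total also gives little away by itself: 56.8% is not far from 50%, and a blinded team does not know past arms at all.

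The scope for selection is limited too. The exclusion criteria are largely numeric cut-offs, named medicines and factual graft types. Under Ethical Considerations, entry depends on meeting the criteria and giving written consent, and no role is named for judging either. The text therefore does not establish that the staff member alone decides who enters. Choosing whom to approach, and when, remains possible in principle.

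Finally, a reader might take the reference to arrival to mean that assignment happens long before the anhepatic-phase infusion, so that cancelled operations leave randomised patients without an outcome. The article does not say whose arrival is meant and gives no interval, so the point cannot rest on this.

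What the reply does not remove is the combination of roles. That is a stated arrangement, not an omitted detail, and calling the person unrelated does not separate the two tasks.

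**Conclusion.** The concern holds in a limited form. As written, the enroller is also the unblinded preparer and knows at least all past allocations, so the arrangement does not assure concealment. A finding that concealment is broken would go beyond the text.

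The size depends on a fact not given. If each assignment is released only after entry and the list has no blocks, predictability is about 57%, with about 2 of 70 assignments certain in advance. If the list can be seen beforehand, every assignment is known. Both figures assume that the two roles are carried out by one person, as the sentence says. There is no inconsistency with the double-blind label: an independent unblinded preparer is compatible with it, but blinding and concealment are different protections.

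The change is worth making because it guards the primary comparison at little cost, and the Results section reports 35 patients recruited, half of the planned 70.

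**What to change.** For the remaining patients, divide the role in two:

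1. A blinded investigator confirms eligibility and consent and registers the patient irrevocably, with a time stamp.
2. Only then is that patient's assignment released to the unrelated staff member, whose sole task is to prepare the infusion.

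Both parts are needed. Release after registration closes off the next assignment. Moving entry to someone blinded removes the knowledge of past arms behind the 56.8%, and guessing returns to 50% for as long as that person stays blind.

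If this is already the practice, one corrected sentence is enough. The cost is a small change of procedure and slightly later preparation. The article does not say who now takes consent, so whether any extra staff time is needed cannot be read from it. The sample size, the sequence and the analysis stay as they are.

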### Analysis

Quantitative variables will be described using mean, median, SD, IQR, 95% CI, and range values. Quantitative data will be presented as absolute and relative frequencies. The significance level in any statistical test will be set at α=.05. Both groups will be assessed to ensure they are balanced in all variables.

A total of 2 populations will be established: one based on intention to treat and the other based on efficacy. The first population will consist of all participants randomized at the start and divided into 2 groups according to the corresponding randomization. The second population will consist of the participants who complete the protocol and end up in the same group in which they were randomized. All analyses will be conducted on both populations; however, the primary analysis will focus on the intention to treat the population. Statistical analyses will be performed using SPSS Statistics.

The comparison between participants who experienced PRS during the intervention will be performed using the chi-square test. Cohort proportions are compared using relative risk with 95% CIs. In a secondary analysis, we will adjust for potentially confounding factors related to the main outcome variable by using a multivariate technique. These factors include variables that showed significant differences (with *P*≤.20) between the control and treatment groups and have been identified as potential confounds. When dealing with binary factors, we will assess the magnitude of association with odds ratios, while for ordinal or quantitative factors, we will use the Spearman correlation coefficient. A binary logistic regression analysis will be conducted to examine the presence of PRS. The control variable (ascorbic acid vs saline) and all variables resulting from the previous univariate analysis will serve as independent variables. The same procedure will be applied to secondary efficacy and safety analyses.

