### Participant Timeline

Patients will be monitored from randomization until day 30 post surgery. The team will collect variables daily through postoperative day 7 and a final visit on postoperative day 30. The research team will closely monitor adverse events, including onset, duration, intensity, progression, and outcome, to assess their relationship to the drug.

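### Safety is compared only by assigned arm or among protocol completers, so no analysis set groups participants by the infusion they received

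*Protocol article*

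**What the plan says.** The Analysis section closes the list of populations: "A total of 2 populations will be established: one based on intention to treat and the other based on efficacy". The first is "all participants randomized at the start and divided into 2 groups according to the corresponding randomization". The second is "participants who complete the protocol and end up in the same group in which they were randomized". Intention to treat is named as primary.

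The scope is then stated without exception: "All analyses will be conducted on both populations". After describing the chi-square test, the relative risk and the adjusted logistic regression, the section adds: "The same procedure will be applied to secondary efficacy and safety analyses".

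Under Participant Timeline, the team follows adverse events in detail "to assess their relationship to the drug". That is an assessment of each event. It gives no rule for grouping participants when the arms are compared.

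**The concern.** An adverse-event comparison is meant to show what happens to people exposed to the drug. Neither stated population is built on exposure. The first follows assignment whatever was given. The second conditions on completing, which happens after treatment and can itself depend on harm.

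A full analysis plan may exist, but this is not a detail that the article simply leaves out. The text fixes the number of populations at two, applies them to every analysis and mentions safety by name. An analysis plan that added an exposure-based set would depart from what is published here.

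At stake is whether the adverse-event table can be read as ascorbic acid against saline. In arms this small, a single event in the wrong column is visible.

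**Working it through.** The plan gives no figure to reproduce, and the documents state no rate of wrong infusions, uninfused participants or adverse events. The check is one of logic, with illustrations under stated assumptions. The only numerical input from the plan is 35 participants per arm (Sample Size Calculation).

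**1. Where each kind of participant is counted**

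| Participant | Intention to treat | Completer set | Grouped by infusion received |
|---|---|---|---|
| Assigned saline, given ascorbic acid | Saline | Excluded | Ascorbic acid |
| Assigned ascorbic acid, given saline | Ascorbic acid | Excluded | Saline |
| Randomized, never infused | Assigned arm | Excluded, if infusion is part of completion | Not included |
| Infusion stopped early for a reaction | Assigned arm | Depends on the meaning of completion | Infusion received |

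The first two rows confirm the gap: neither stated population puts such a participant under the drug received.

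**2. One misplaced event.** Suppose one participant assigned to saline receives ascorbic acid and has the only event in the trial, and everyone else completes as assigned.
- Intention to treat: ascorbic acid 0/35 = 0%, saline 1/35 = 2.9%.
- Completer set: 0/35 against 0/34.
- By infusion received: ascorbic acid 1/36 = 2.8%, saline 0/34 = 0%.

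**3. Wrong infusions in both arms.** Let k participants in each arm receive the other infusion, with event rates p_d on the drug and p_s on saline, and with the error unrelated to risk.
- Intention-to-treat difference = [(35 − k)p_d + k·p_s]/35 − [(35 − k)p_s + k·p_d]/35 = (1 − 2k/35)(p_d − p_s).
- k = 1: 33/35 = 94% of the difference by drug received. k = 2: 31/35 = 89%. k = 3: 29/35 = 83%. k = 4: 27/35 = 77%.
- With assumed rates of 20% and 5% and k = 2: 0.886 × 15.0 = 13.3 points instead of 15.0.

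**4. Never infused.** Assume that uninfused participants have no counted events and that the rate among infused participants is 10%.
- One uninfused in the arm: 34 × 0.10 = 3.4; 3.4/35 = 9.7%.
- 10% uninfused (a pure assumption): 31.5 × 0.10 = 3.15; 3.15/35 = 9.0%.
- If the same share is uninfused in both arms, the relative risk does not move. For example, 10%/5% = 2 and 9%/4.5% = 2. The absolute rates and their difference shrink.

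**5. Stopped for a reaction.** One such participant on ascorbic acid, with no other events, gives 1/35 = 2.9% by intention to treat, in the correct arm. In the completer set the result is 0/34 if stopping counts as not completing. It is 1/35 if completion means reaching the day 30 visit. The article does not say which.

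**The case against.** The strongest reply is that the problem may never arise. Treatment is a single 30-minute infusion in the anhepatic phase, given double-blind and prepared by an unrelated staff member. No crossover or repeat dosing is described. A wrong infusion would need a preparation error, and the wording of the second population reads like a conventional per-protocol definition rather than a forecast of switching. Case-by-case causality assessment could also link an event to the drug given. This reply stands as to frequency. It does not repair the group comparison, because causality review sets no denominator and moves no one between columns.

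Some stronger readings are tempting but unsupported:
- A reader might infer that both stated safety analyses must err toward showing no harm. Wrong infusions do pull the intention-to-treat difference toward zero on average. Uninfused participants, however, can leave the relative risk unchanged, and dropping non-completers from both arms has no fixed direction.
- A reader might infer that an infusion reaction that stops treatment disappears. It can leave only the completer set. Intention to treat, the primary set, keeps it in the assigned arm.
- A reader might take the 10% loss rate in the sample-size section as the expected share never infused. It belongs to the 268-participant calculation, and nothing places those losses before the infusion.
- A reader might tie the stakes to the Discussion's remark about few side effects. That remark concerns patients with sepsis. The case for a larger trial rests on efficacy results.

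**Conclusion.** The point holds as a real but modest defect in a stated rule. Every safety comparison is either by assigned arm or restricted to completers, so none reflects the infusion received, and one of the two can lose participants because they were harmed.

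One misplaced event is 2.9 points in an arm of 35. One or two wrong infusions per arm would shrink the risk difference to 94% or 89% of its value by drug received. These sizes rest on assumed counts, since the documents give none. The direction of the overall bias is not established. The effect through the completer set depends on an undefined notion of completion. If everyone is infused as assigned, intention to treat already gives the exposure-based answer and only the completer-set weakness remains.

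It does not follow that acute kidney injury and renal replacement therapy should leave the randomized comparison. The plan lists both as secondary variables, and intention to treat should remain primary for them.

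**What to change.** - Add a third population for safety: all participants who received any part of the study infusion, grouped by the infusion actually received. Make it the primary set for adverse events.
- State that the completer set will not be used for safety conclusions.
- Keep intention to treat as primary for postreperfusion syndrome and every listed secondary variable. For acute kidney injury and renal replacement therapy, add an as-received analysis as supportive only.

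The cost is a few sentences and one population flag. Two things must be accepted. The adverse-event comparison is no longer strictly by randomization if anyone was switched. The infusion actually given must also be recorded for each participant; the article mentions a preparer but no such record, so this should be confirmed. If no one is switched or left uninfused, the new set is identical to intention to treat and nothing is lost.

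### The secondary adjusted PRS model picks covariates by a between-arm P≤.20 screen, which selects on chance imbalance rather than prognosis and leaves the model unknown until the data are seen

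*Protocol article*

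**What the plan says.** The Analysis section of the protocol article makes an unadjusted chi-square test, with a relative risk and 95% CI, the main comparison for PRS, with the intention-to-treat population as the primary focus. Adjustment is placed in a secondary analysis.

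- **Balance check.** "Both groups will be assessed to ensure they are balanced in all variables".
- **Selection.** Of the factors to adjust for, the section says: "These factors include variables that showed significant differences". The threshold is P≤.20 between the control and treatment groups, and the variable must also count as a potential confounder.
- **Entry.** A binary logistic regression for PRS follows: "The control variable (ascorbic acid vs saline) and all variables resulting from the previous univariate analysis will serve as independent variables".
- **Reach.** The same steps apply to the secondary efficacy and safety analyses.

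The article shows neither a list of candidates nor a limit on how many may enter. The Sample Size Calculation section gives 35 participants per arm, a PRS incidence of 30% at the center and an assumed 15% under ascorbic acid.

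**The concern.** A test of baseline differences between randomised arms tells the analyst nothing about which variables predict the outcome. The null hypothesis of that test is true by design, so a P≤.20 threshold passes about one candidate in five, prognostic or not. A strong predictor of PRS that happens to be balanced is left out, although adjusting for it would gain power. An irrelevant variable that happens to be imbalanced is put in, and because it is correlated with treatment in the sample it costs precision.

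Two features make this matter more here. PRS events are few, so the model can carry little. The Sample Size Calculation section also presents the trial as groundwork for a multicenter trial even if significance is not reached, so readers will look at the size of the estimated effect. An adjusted odds ratio whose covariates are settled only after the data are seen is weak support for that decision.

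**Working it through.** **Inputs.** Control incidence 30%, treated incidence 15% and 35 per arm (Sample Size Calculation); threshold P≤.20 and entry of all selected variables (Analysis). The number of candidates K is not given, so K = 5, 10, 20 and 30 are assumptions.

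**The plan's own figure.** The article states no event count. The nearest stated figure is the unrestricted sample size: "we require 268 participants (134 in each group", from "an α risk of 5% and a power of 80%, bilateral testing, and the Fleiss correction with a 10% loss rate". With p̄ = 0.225,

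n = [1.96·√(2·0.225·0.775) + 0.842·√(0.30·0.70 + 0.15·0.85)]² / 0.15² ≈ 121 per arm.

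The continuity correction alone gives 134. The loss allowance alone gives 121 × 1.1 = 133.1, also 134 after rounding up. Both together give 134/0.9 ≈ 149. So 134 per arm matches these rates with one of the two allowances, not both. That is a separate matter and does not alter the event counts below.

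**Expected PRS events with 70 participants.**
- 30% vs 15%: 35 × 0.30 + 35 × 0.15 = 15.75
- No effect: 35 × 0.30 × 2 = 21
- Complete elimination: 35 × 0.30 + 0 = 10.5

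**What the screen selects.** Each baseline candidate passes with probability 0.20. For independent candidates the expected number selected is 0.20·K, and the chance that at least one is selected is 1 − 0.8^K.

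**Events per parameter**, counting treatment: 15.75/(1 + number selected). One covariate gives 15.75/2 = 7.9; two give 15.75/3 = 5.3.

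| K (assumed) | Mean selected | P(at least one) | Events per parameter at the mean |
|---|---|---|---|
| 5 | 1 | 0.67 | 7.9 |
| 10 | 2 | 0.89 | 5.3 |
| 20 | 4 | 0.99 | 3.2 |
| 30 | 6 | 0.999 | 2.3 |

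**Power, by simulation.** 35 vs 35, PRS 30% vs 15%, K standard-normal candidates of which two are prognostic (log odds ratio 0.7 per SD, assumed), t-test screen at P≤.20, all selected variables entered, Wald test of treatment.

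| K | Screened model | Unadjusted | Two prognostic covariates fixed in advance |
|---|---|---|---|
| 5 | 29% | about 30% | 32–33% |
| 10 | 28% | about 30% | 32–33% |
| 20 | 26–28% | about 30% | 32–33% |
| 30 | 26% | about 30% | 32–33% |

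A given prognostic covariate was included in 19–20% of trials. For 4,000 trials, the simulation standard error near 30% is √(0.3 × 0.7/4000) = 0.7 points, so the gap from unadjusted at K = 5 is hardly distinguishable from none.

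**Candidates that are all noise** (4,000 trials per setting; true log odds ratio −0.89). The mean adjusted log odds ratio was −0.97, −1.01 and −1.06 for K = 10, 20 and 30, against about −0.93 unadjusted. Its SD was 0.73, 0.80 and 0.88, against about 0.65. With PRS at 22.5% in both arms, rejection was 4.4%, 5.4% and 5.3% with the screen, against 4.1%, 4.9% and 4.2% without it.

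The SD comparison is meaningful only in this all-noise setting. When covariates are prognostic, a sound prespecified model also has a log odds ratio SD of about 0.75–0.79, so a larger SD alone does not show harm.

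**The case against.** **The analysis is secondary.** This stands. The chi-square test and relative risk do not use the model, and the article itself concedes limited power. A reader might infer that the trial's main result is compromised or that false positives are inflated. The document does not support the first, and the simulated null rejection rates do not clearly show the second.

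**The screen is not the only condition.** The text also requires that a variable count as a potential confounder, speaks of factors related to the main outcome, and mentions odds ratios and Spearman correlations as measures of association. This may narrow the pool, and it stands as a limit on how many covariates would enter. It does not rescue the rule, because a balanced prognostic variable still fails the P≤.20 condition.

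**Overfitting depends on an assumed K.** This stands too. With five candidates the model typically carries one covariate and behaves much like the unadjusted one. Severe overfitting is a possibility, not an established fact. A candidate list or a cap may sit in an analysis plan not shown, so their absence is not the point; the stated selection rule is.

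**Zero events.** A reader might infer that the logistic odds ratio will fail to exist because the treated arm could have no PRS. The article calls complete elimination unlikely. At its assumed 15%, the chance of no events in 35 is 0.85^35 = 0.3%. This is no ground for the point.

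**Conclusion.** The point holds as a should-fix on a stated rule. In a randomised comparison, selecting covariates by between-arm P-values is the wrong criterion, and entering whatever passes makes the adjusted estimate depend on chance imbalance. The cost in power is about 1 to 4 points against no adjustment and about 3 to 7 points against two well-chosen prespecified covariates. The estimate also drifts somewhat away from the null when many irrelevant variables enter.

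These sizes rest on the article's 30% and 15%, on assumed candidate counts, on independent candidates measured at baseline, and on the assumed prognostic strength. The chance argument applies to the groups as randomised. In the efficacy population, differences may also reflect who completed the protocol, which gives no better reason to select by P-value. For secondary and safety outcomes the same flaw applies; its size was not calculated, and outcomes with fewer events would tolerate fewer covariates.

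**What to change.** In the Analysis section, delete the P≤.20 between-arm screen and describe baseline balance without using tests to choose covariates. Before unblinding, name one or two baseline variables chosen on clinical grounds for their relation to PRS, and enter them with treatment whatever their observed balance. At the assumed rates this fixes the model at 7.9 or 5.3 events per parameter, so the limit of two should be kept. Apply the same principle to the secondary efficacy and safety models, with the number of covariates suited to the events expected for each outcome. Penalised (Firth) logistic regression may be named as an optional fallback if an arm has no events; it may need an SPSS extension or other software.

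The cost is one paragraph of wording and the investigators' commitment to the variables before the database is opened. Nothing in recruitment, treatment or data collection changes, provided the chosen variables are already recorded at baseline. At publication 35 patients had been recruited and the analysis was still ahead.
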